#### Outcomes ascertainment

The primary and secondary outcomes will be collected and analyzed in an independent and blinded manner by research personnel who have not been involved in the patient's care and will be blinded to patient's randomization group and baseline measurements (including BPs). Thus, although patients and their physicians cannot be masked to the fact that they are in the intervention arm, those collecting outcome data and analyzing the data will be blinded.

Systolic BP will be ascertained at baseline and at six months using the BPTru^® ^device. All study-related lab measurements, collected at baseline, six, and 12 months, will be drawn and independently analyzed at one central lab (Dynalife Dx, Edmonton, Alberta, Canada). All survey instruments will be administered locally at baseline, 6, and 12 months, but collated and analyzed at one central lab, the Epidemiology Coordinating and Research (EPICORE) Centre, Division of Cardiology, University of Alberta. Clinical events reported by patients, their family members, or their primary care physicians will be independently validated by the central outcome validation committee that will be blinded to patients' allocated treatment arms. All patients will be asked to sign the appropriate consent and privacy forms needed to permit examination of clinical outcomes, resource use, and vital status at six months and one year (to cross-check and validate data collected at the active follow-up appointments), and at five and ten years, to gain further insights into long-term clinical event rates.

#### Sample size

In a survey of members of the divisions of neurology and general internal medicine at the University of Alberta, we determined that the 'minimal' clinically important difference for this particular intervention to be considered useful was a 10% absolute improvement in the proportion of patients achieving 'optimal BP and lipid control' over and above usual care. After six months, we estimate that no more than 5% of control patients will have attained our composite primary outcome (given that patients who are at goal BP and lipid levels at baseline will be excluded from this study). We calculated our sample size to detect a 10% absolute increase in the primary outcome, set the alpha error rate at 0.05 (2-sided), and the beta error at 0.20 (power 80%); this yielded a minimal necessary sample size of 140 patients per study arm.

The calculated sample size will also provide 80% power (assuming a standard deviation of 15 mm Hg, as recently found in our trial of diabetic hypertensive patients) [34] to detect a 5 mm Hg between-group difference in systolic BP at six months with alpha of 5% for a two-sided test. Based on a review of the literature, consensus of the investigators, and consensus of over two dozen members of the Evidence-Based Recommendations Task Force of the Canadian Hypertension Education Program (surveyed by [name], in his role as Chair of the Central Review Committee for the Evidence-Based Recommendations Task Force of the Canadian Hypertension Education Program]), a 5 mmHg sustained difference in SBP, over and above usual care, would be considered clinically meaningful.

A sample size of 140 patients per group will also provide 85% power (assuming a standard deviation of 0.84 mmol/L, as recently found in our trial in patients with coronary disease) [35] to detect a 0.3 mmol/L between-group difference in fasting LDL cholesterol at six months with alpha of 5% for a two-sided test. This sample size will also provide 85% power (assuming a standard deviation of 14%, as recently found in a trial of 2,687 patients) [53] to detect a 5% between-group difference in projected five-year risk of cardiovascular disease at six months with alpha of 5% for a two-sided test.

One interim analysis is planned, when 140 patients (50% of the projected minimum sample) have had their six-month outcomes ascertained. An independent data and safety monitoring board will examine whether our assumptions about changes in BP and lipid levels (as well as standard deviations) are consistent with the data at that time and will make a recommendation to the study steering committee about whether or not we should continue the study as planned, increase enrollment, or stop the study due to futility. Although we had initially proposed a total sample size of 340 (reflecting a 20% inflation above the minimum necessary sample size to account for potential losses to follow-up), in our most recent trial of 480 patients with coronary artery disease, losses to follow-up were only 3% due to the new province-wide electronic health record in Alberta. Thus, we will examine losses to follow-up in the first 140 patients randomized to determine how much 'inflation factor' we must apply to the sample size to ensure we have outcomes for at least 140 patients per arm at 6 months.

### Statistical analysis

All sociodemographic and clinical characteristics at baseline and follow-up will be summarized using percentages for categorical variables and medians (interquartile range) for continuous variables. Chi square tests will be used to compare the proportion of patients who attain 'optimal BP and lipid control' at six months (because the proportion at baseline will be zero by definition), as well as other binary secondary outcomes such as proportions that achieve target BP and lipid levels. Patient and health system factors associated with meeting BP and lipid goals will be assessed in multivariate analyses. To compare changes in systolic BP, LDL cholesterol, and total:HDL cholesterol ratios between intervention and control, we will use 2-sample independent t-tests. In the event that any baseline characteristics are not balanced between study groups, we will employ multivariate extensions of our primary analytic plan (*i.e*., substituting multiple linear regression for t-test or multiple logistic regression for Chi square test), adjusting for any clinically important (*i.e*., greater than 10% imbalance between arms) or statistically significant (*i.e*., p-value of < 0.10 between arms) differences observed between groups.

All analyses will be by intention to treat. Missing data at the six-month follow-up assessment will be imputed with a 'baseline-observation carried forward' strategy; this approach conservatively assumes that all subjects lost to follow-up have had no change in their BP or lipid levels. As a sensitivity analysis for this assumption, we will also analyze the data in an 'on-treatment' analysis, using only those cases with complete follow-up data for each analysis.

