**Methods:**

We will conduct a prospective, randomized, controlled open-label with blinded ascertainment of outcomes (PROBE) trial. Treatment allocation will be concealed from the study personnel, and all outcomes will be collected in an independent and blinded manner by observers who have not been involved in the patient's clinical care or trial participation and who are masked to baseline measurements. Patients will be randomized to control or a pharmacist case manager treating vascular risk factors to guideline-recommended target levels. Eligible patients will include all adult patients seen at stroke prevention clinics in Edmonton, Alberta after an ischemic stroke or TIA who have uncontrolled hypertension (defined as systolic blood pressure (BP) > 140 mm Hg) or dyslipidemia (fasting LDL-cholesterol > 2.00 mmol/L) and who are not cognitively impaired or institutionalized. The primary outcome will be the proportion of subjects who attain 'optimal BP and lipid control'(defined as systolic BP < 140 mm Hg and fasting LDL cholesterol < 2.0 mmol/L) at six months compared to baseline; 12-month data will also be collected for analyses of sustainability of any effects. A variety of secondary outcomes related to vascular risk and health-related quality of life will also be collected.

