### Study participants

Patients older than 18 years of age, with a stroke or TIA, who are evaluated at a SPC are eligible for the study if they are confirmed by a stroke specialist to have had an ischemic stroke or TIA within the past year and have systemic hypertension (average systolic BP over two visits exceeding 140 mmHg), fasting LDL cholesterol exceeding 2.0 mmol/L, or total:high-density lipoprotein (HDL) cholesterol ratio exceeding 4.0.

Patients will be excluded if any one of the following criteria apply:

1. Neurological event considered to be due to hemorrhage (*e.g*., intracranial hemorrhage, subarachnoid hemorrhage), cardiac embolus related to structural heart disease (valve abnormality, atrial or ventricular septal defect, endocarditis), or trauma (as defined by stroke specialists).

2. Participation in a concurrent trial related to stroke or vascular disease.

3. Any condition that would preclude treatment benefit or 12-month follow-up, including foreshortened life-expectancy (*e.g*., active malignancy), hypertensive urgency (clinic systolic BP ≥200 mm Hg), or severe comorbidities.

4. Institutionalized in a long-term care facility.

5. Impaired cognition (scored ≥5 on the Short Portable Mental Status questionnaire) [50].

6. Refractory hypertension or hyperlipidemia (levels uncontrolled despite already being on three antihypertensive drugs at maximal dose if hypertension is their inclusion criterion, or on maximal dose statin if hyperlipidemia is their inclusion criterion).

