#### Screening

After initial assessment in participating SPCs (which will include standard SPC workup, including collection of data elements for the ABCD^2 ^score [55], carotid dopplers, CT scan, fasting lipid profile, fasting glucose, electrolytes, creatinine, complete blood count (CBC), liver function tests, glycosylated hemoglobin, and electrocardiogram), all potentially eligible patients who consent to further screening for the trial will be assessed in person at a study screening visit within two weeks by a research assistant. At this visit, they will have their BP measured using the BpTRU^® ^device (VSM MedTech, Vancouver, BC, Canada). If their average systolic pressure (averaged between the SPC measurement and the average measurement at the study screening visit) exceeds 140 mm Hg or their fasting lipid profile reveals LDL cholesterol exceeding 2.0 mmol/L or total:HDL cholesterol ratio > 4, and they provide written consent for the study, baseline case report forms will be completed.

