#### Primary outcome

Because hypertension and dyslipidemia are the most important risk factors for recurrent cardiovascular events in patients with ischemic stroke or TIA [5,57,58], a composite outcome incorporating both has been selected as the primary study outcome. Specifically, the primary outcome is the proportion of subjects who attain 'optimal BP and lipid control'(defined as systolic BP ≤140 mm Hg and fasting LDL cholesterol ≤2.0 mmol/L) at six months according to allocation status.

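### Entry on the total:HDL ratio alone admits patients who already meet the primary outcome, which contradicts the stated zero baseline and the basis of the 5% control rate

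*Protocol article*

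**What the plan says.** - **Entry.** Study participants admits a patient with a qualifying event on any one of three findings: average systolic BP over two visits above 140 mm Hg, "fasting LDL cholesterol exceeding 2.0 mmol/L, or total:high-density lipoprotein (HDL) cholesterol ratio exceeding 4.0". Screening repeats the ratio as a sufficient alternative. None of the six exclusions removes a patient whose SBP and LDL are both at goal.
- **BP used for entry.** Screening takes the mean of two occasions, "averaged between the SPC measurement and the average measurement at the study screening visit". Outcomes ascertainment says SBP at baseline and at six months is taken with the BpTRU device.
- **Primary outcome.** Attainment of control is "defined as systolic BP ≤140 mm Hg and fasting LDL cholesterol ≤2.0 mmol/L". The ratio target appears only among the secondary outcomes.
- **Sample size.** The control rate is put at 5% at most, "given that patients who are at goal BP and lipid levels at baseline will be excluded from this study".
- **Analysis.** A chi-square test compares the arms at six months only, "because the proportion at baseline will be zero by definition". Missing six-month values take the baseline value.
- **Abstract, Methods.** The risk-factor criteria there are "uncontrolled hypertension (defined as systolic blood pressure (BP) > 140 mm Hg) or dyslipidemia (fasting LDL-cholesterol > 2.00 mmol/L"); no ratio route is mentioned.

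**The concern.** Entry has three routes and the primary outcome has two components. A patient who qualifies by the third route alone is, by construction, not above goal on either outcome component. Two statements that carry weight then fail under the plan's own rules: that nobody is at goal at baseline, and that at-goal patients are kept out and so hold the control rate at 5% or below.

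Patients already at goal tend to count as successes in both arms whatever the intervention does. They raise the control rate, which increases the variance of the comparison, and they shrink the difference the intervention can produce. The result also becomes harder to read, because some of those reported as attaining control had it when they were randomised.

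**Working it through.** **1. Can a patient be eligible and already at goal?**

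Take total cholesterol 3.6, HDL 0.8 and LDL 1.9 mmol/L, with SBP 130 mm Hg. The ratio is 3.6 / 0.8 = 4.5, above 4, so the patient is eligible. LDL is not above 2.0 and SBP is not above 140, so the primary outcome is met at entry. Under the Abstract's two routes this patient would not be admitted.

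**2. The averaged-BP rule (conditional).**

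Take a clinic SBP of 150 and a screening SBP of 134. The mean is (150 + 134) / 2 = 142, so the patient is eligible. If baseline SBP is the screening BpTRU value (134) and LDL is 2.0 or below, this patient too is at goal at baseline. If baseline SBP is the qualifying mean (142), the patient is not. The document does not say which value is baseline.

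**3. The plan's own sample size.**

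Inputs from Sample size: control 5%, intervention 15%, two-sided alpha 0.05, power 80%, 140 per arm. With the pooled-variance formula and p̄ = 0.10:

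n = [1.96·√(2·0.10·0.90) + 0.8416·√(0.05·0.95 + 0.15·0.85)]² / 0.10² = (0.8315 + 0.3521)² / 0.01 = 140.1

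This rounds up to 141 per arm, and power at 140 is 0.80. The plan's figure is reproduced, so the arithmetic is sound and the question is the 5% premise.

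**4. Effect of at-goal entrants.**

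Let f be the share of randomised patients at goal at baseline and m the share of those still at goal at six months. Neither is in the document; both are assumed equal in the two arms. The other patients behave as planned:

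- control rate = f·m + (1 − f)·0.05
- intervention rate = f·m + (1 − f)·0.15
- difference = (1 − f)·0.10

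| f | m | Control | Intervention | Power at 140/arm | n/arm for 80% |
|---|---|---|---|---|---|
| 0 | – | 5.0% | 15.0% | 0.80 | 141 |
| 2% | 1.0 | 6.9% | 16.7% | 0.72 | 169 |
| 2% | 0.6 | 6.1% | 15.9% | 0.75 | 159 |
| 5% | 1.0 | 9.75% | 19.25% | 0.62 | 215 |
| 5% | 0.6 | 7.75% | 17.25% | 0.67 | 190 |
| 10% | 1.0 | 14.5% | 23.5% | 0.48 | 298 |
| 10% | 0.6 | 10.5% | 19.5% | 0.56 | 246 |

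Most of the loss comes from the higher control rate. At f = 5% and m = 1, keeping the full 10-point difference still gives power of only 0.66.

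**5. Size of the conditional BP route.**

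This is a simulation on assumed values: true SBP mean 145, between-patient SD 14, visit SD 10 mm Hg. Among patients whose two-visit mean exceeds 140, about 11% have a screening value of 140 or below (19% if clinic readings run 10 mm Hg higher). That is only the BP half of the composite. The Background reports that 77% of clinic patients missed the LDL target at baseline, leaving 23% at target. If LDL is independent of BP, the at-goal share among all entrants by SBP or LDL is about 1.8% (3.5% with the offset). In the same model, only about 36% (45%) of the BP-qualified patients with a low screening value would read 140 or below again at six months without any change in treatment.

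**6. Carry-forward.**

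A lost patient who was at goal at baseline is imputed as a success. With the 3% loss that the protocol reports from the group's recent coronary trial, and f = 5%, this is 0.03 × 0.05 = 0.15% of patients, or 0.0015 × 280 ≈ 0.4 of a patient.

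**The case against.** The strongest reply is that the comparison remains valid. Allocation is randomised, so a six-month chi-square test between arms keeps its type I error whatever the baseline rate. The remark about a zero baseline can be wrong without making the test wrong. That stands: a reader might infer that the primary test is invalidated, and the document does not support this.

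A reader might also infer that the averaged-BP rule certainly admits at-goal patients, and might carry the 11% from step 5 to the 10% row of the power table. Neither step is supported. The route exists only if baseline SBP is the single screening reading, which the document leaves open. The 11% omits the LDL condition, and many of these patients would drift back above 140, so full retention is a worst case for them.

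Further, f for the ratio route is unknown and may be small; at 2% the loss of power is modest. The planned interim review of the BP and lipid assumptions can recommend more enrolment. That is partial mitigation, but it does not correct the entry rule or the analysis statement. The carry-forward point is minor if losses are low.

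None of this removes the contradiction over the ratio route, which needs no outside figure to establish.

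**Conclusion.** The point holds for the ratio route. As written, the entry criteria admit patients who already meet the primary outcome. This contradicts the zero-baseline statement in Statistical analysis, the premise for the 5% control rate in Sample size, and the Abstract's entry criteria. For the averaged-BP rule the point holds only if baseline SBP is the screening BpTRU value.

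What suffers is power, the basis of the sample size and the interpretation of the outcome. The size cannot be fixed from the document. The power ranges in step 4 are illustrations: they assume a share f of 2% to 10%, 60% to 100% of those patients still at goal at six months, the same f and retention in both arms, and all other patients behaving as planned. They are not estimates of this trial's power.

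**What to change.** Reconcile the Abstract, Study participants, Screening, Primary outcome, Sample size and Statistical analysis in one of two ways:

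1. **Align entry with the SBP/LDL composite**, as in the Abstract, and keep the ratio as a secondary outcome. For the ratio route, this restores the stated premise. The cost is slightly slower recruitment.
2. **Keep the ratio route.** Analyse all randomised patients with prespecified adjustment for baseline goal status, and restate the control rate and power with a justified share at goal at baseline. The cost is probably a larger sample.

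In both cases, state which SBP is the baseline value, delete the statement that baseline attainment is zero, and report baseline attainment by arm. These are changes of wording and reporting only.

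An analysis restricted to patients not at goal at baseline can be added as support. It need not displace the intention-to-treat analysis of all randomised patients.

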### Current stroke prevention practices

A recent analysis of data on over 2,000 patients evaluated in the SPC at the University of Alberta Hospital (Edmonton, Canada) confirmed the suboptimal management of vascular risk factors in patients with recent stroke or TIA in our health region [7,8]. Treatable risk factors (hypertension and dyslipidemia) for stroke were seen in over 80% of patients, and the vast majority of these patients were not controlled to recommended targets at any point during the first year after being seen in our SPC [8]. Furthermore, there did not seem to be any substantial improvement in risk factor management in our health region over the four years encapsulated within the pilot data collection [7,8], nor in the intervening three years since their publication. An analysis of the electronic database maintained by Alberta Health Services for SPC patients up to July 2008 revealed that 77% of patients at baseline (and 68% at follow-up) did not meet currently recommended low-density lipoprotein (LDL) cholesterol targets for stroke/TIA patients of ≤2.0 mmol/L ([name], Chair of the Evaluation and Quality Improvement Pillar of the Alberta Provincial Stroke Strategy, personal communication, August 18, 2008), suggesting little change will occur outside of a targeted intervention.

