#### Secondary outcomes

Secondary outcomes will include change in systolic BP at six months versus baseline, proportion achieving BP target (SBP ≤140 mmHg), change in LDL cholesterol at six months versus baseline, proportion attaining LDL cholesterol targets (LDL ≤2.0 mmol/L), proportion attaining total:HDL cholesterol ratios ≤4.0, changes in the cardiovascular disease life expectancy model score [53], changes in other vascular risk factors (waist circumference, body-mass index, self-reported smoking rates, and physical activity), and therapy changes (including number, dosing, and self-reported adherence with antihypertensive and lipid lowering agents). Although differences in clinical events are not anticipated given the short duration of this trial, data will be collected on all-cause hospitalizations, emergency room visits, primary care physician visits, mortality, and clinical events (confirmed by an independent outcome validation committee, blinded to allocation status) such as stroke, TIA, MI, or revascularization. We will also examine humanistic outcomes such as changes in EUROQOL(EQ)-5D [59] and the modified Rankin scale [60] in intervention versus control patients over the course of the trial and will collect direct and indirect costs to conduct a formal cost-effectiveness analysis if the intervention is efficacious. Finally, in order to explore the sustainability of any changes induced by the six-month intervention, we will examine changes in the primary and secondary outcomes at twelve months in both study arms (*i.e*., six months after the intervention stopped). Note that all data will be collected during active follow-up in the twelve-month study period, and further clinical event data will be collected by passive follow-up (for up to five years) through annual linkage to provincial physician billing databases/Canadian Institute for Health Information (CIHI)/provincial vital statistics and registered persons databases after completion of this study as per prior studies by our group [61].

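### Single-factor target outcomes use an unadjusted chi-square with an imbalance-triggered switch, which is valid but gives up precision that always adjusting for the baseline value would recover

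*Protocol article*

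**What the plan says.** Under Statistical analysis, the protocol compares the proportion attaining the composite at six months by chi-square, with the reason "because the proportion at baseline will be zero by definition". The same sentence gives that test to "as well as other binary secondary outcomes such as proportions that achieve target BP and lipid levels". Secondary outcomes lists these as "proportion achieving BP target (SBP ≤140 mmHg"), "proportion attaining LDL cholesterol targets (LDL ≤2.0 mmol/L") and a total:HDL ratio of 4.0 or less.

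Baseline enters these analyses only conditionally. If arms turn out unbalanced, the plan allows "substituting multiple linear regression for t-test or multiple logistic regression for Chi square test", adjusting for differences that are clinically important, "greater than 10% imbalance between arms) or statistically significant" at p < 0.10.

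Under Study participants, a patient qualifies on raised systolic pressure, "fasting LDL cholesterol exceeding 2.0 mmol/L, or total:high-density lipoprotein (HDL) cholesterol ratio exceeding 4.0". One abnormal value is enough.

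**The concern.** A patient enrolled on LDL alone can already have SBP at or below 140 mm Hg, and one enrolled on SBP alone can already have LDL at or below 2.0 mmol/L. For a single-factor outcome, being at target at six months therefore mixes patients who got there with patients who began there. The baseline value, measured in everyone, helps to predict which patients will be at target, whichever arm they are in.

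The default test does not use that information. The switch brings it in only when the arms happen to differ on it, and observed imbalance is a poor guide to whether a covariate is worth including. What is at stake is the width of the intervals on the outcomes that help to show whether blood pressure or lipids drive any effect on the composite.

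**Working it through.** **The plan's own figures.** For 5% v 15%, two-sided alpha 0.05 and 80% power:

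n = [1.960·√(2·0.10·0.90) + 0.842·√(0.05·0.95 + 0.15·0.85)]² / 0.10² = (0.832 + 0.352)² / 0.01 ≈ 140.1, so 141 per arm.

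Power at 140 per arm is 80.0%. The same size gives 79.6% for 5 mm Hg with SD 15 (stated 80%) and 84.8% for 0.3 mmol/L with SD 0.84 (stated 85%). The Sample size section reproduces.

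**Inputs for the check**
- From Sample size: 140 per arm; SBP SD 15 and effect 5 mm Hg; LDL SD 0.84 and effect 0.3 mmol/L.
- From Current stroke prevention practices: "77% of patients at baseline (and 68% at follow-up) did not meet currently recommended low-density lipoprotein (LDL) cholesterol targets", so about 23% were at target at baseline. These are clinic patients, not the trial sample.
- Assumed: baseline SBP mean 140 (50% at target), control fall 3 mm Hg; control LDL fall 0.2 mmol/L; normal values; baseline-to-six-month correlation r = 0.3, 0.5 or 0.7. The documents give no correlation.

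**Attainment at six months**, Φ((target − mean)/SD):
- SBP control: Φ((140 − 137)/15) = Φ(0.20) = 0.579. Intervention: Φ((140 − 132)/15) = Φ(0.53) = 0.703.
- LDL baseline mean: 2.0 + 0.739 × 0.84 = 2.62. Control: Φ((2.0 − 2.42)/0.84) = 0.308. Intervention: Φ((2.0 − 2.12)/0.84) = 0.443.

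**Unadjusted power for SBP, in closed form.** Difference 0.703 − 0.579 = 0.124; pooled proportion 0.641. The null SE is √(0.641·0.359·2/140) = 0.0573 and the alternative SE is √((0.579·0.421 + 0.703·0.297)/140) = 0.0569. Power is Φ((0.124 − 1.96·0.0573)/0.0569) ≈ Φ(0.20) = 0.58. The simulated chi-square agrees.

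**Chi-square v logistic regression on arm plus continuous baseline value, by simulation:**

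| | r = 0.3 | r = 0.5 | r = 0.7 |
|---|---|---|---|
| SBP target: chi-square (about 58-59% throughout), then adjusted | 60% | 65% | 75% |
| LDL target: chi-square (about 64-67% throughout), then adjusted | 66% | 73% | 80% |
| Risk-difference variance, unadjusted/adjusted | 1.05 | 1.17 | 1.45 |

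The variance ratios equate to 140 × 1.05 = 147, 140 × 1.17 = 164 and 140 × 1.45 = 203 patients per arm under the unadjusted analysis. With no true effect, type I error stays near 5% for both tests.

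**What the switch recovers.** Under sound randomisation a p < 0.10 criterion is met for any one measure in about 10% of trials, so about 90% keep the chi-square on that account. Following the p < 0.10 rule adds about 0 to 2 power points over never adjusting.

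The scale of the 10% criterion is not stated. On the LDL mean, 10% is 0.262 mmol/L against an SE of 0.84·√(2/140) = 0.100, or 2.6 SE, which adds nothing to p < 0.10. As 10 percentage points on a 50% at-target rate, it is 0.10/√(2·0.25/140) = 1.67 SE, again met in about one trial in ten. A relative reading of that rate (5 points, 0.84 SE) would be met more often, so the 10% figure belongs to the p < 0.10 arm.

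**Limits of the check.** Clinic was not in the simulated model, the eligibility cut-offs were not imposed on the baseline distribution, and total:HDL was not simulated because the documents give no SD or effect for it.

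**The case against.** The best defence is that nothing here is invalid. Randomisation alone justifies a two-arm chi-square on six-month proportions, and its standard error already allows for chance baseline differences. The outcomes are secondary and carry no power claim. The continuous changes in SBP and LDL also show which factor is moving, and they have stated power of 80% and 85%. The gain from adjustment rests on a correlation that the documents do not give, and at 0.3 it is only about 2 points. All of that stands, and it limits the point to a free improvement.

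Two stronger readings are tempting, and the text supports neither.
- *That baseline is ignored.* It is not: a marked imbalance in baseline SBP or LDL would trigger very nearly the model recommended here. Only the default omits baseline.
- *That the plan justifies these tests by a false claim of zero attainment at baseline.* The zero-at-baseline remark is a parenthesis attached to the composite, placed before the other binary outcomes are mentioned. The plan does not assert it for them.

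It can also be said that covariate lists belong in an analysis plan that is not shown. That would answer a complaint of silence. Here the article states both the default test and the rule for leaving it, and that rule can be judged as written.

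**Conclusion.** The point holds as a loss of precision on secondary binary outcomes. A reader might infer bias or an inflated error rate, but type I error near 5% for the chi-square rules that out. The primary outcome and its sample size are unaffected.

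Always adjusting gains about 2 power points at r = 0.3, 6 to 7 at r = 0.5 and 14 to 16 at r = 0.7. The imbalance rule, at its p < 0.10 trigger, recovers 0 to 2 of these. The direction does not depend on the exact inputs. The size rests on the assumed correlation, baseline means and control-arm falls, and on clinic data for the share already at the LDL target.

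**What to change.** For each single-factor target (SBP, LDL, total:HDL ratio), prespecify logistic regression on arm, the patient's own continuous baseline value of that measure, and stroke prevention clinic, which is already the randomisation stratum. Use it whatever imbalance is observed, in place of both the chi-square and the imbalance-triggered switch. Report the standardised risk difference with its 95% CI.

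The zero-at-baseline remark needs no retraction on this account, since it is made only for the composite. The cost is a sentence or two of analysis wording; all the baseline values are already collected and no extra patients are needed.
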